### Sample size

The sample size needed for the study was determined based on information on the effect size. We needed the participation of 20 GPs, each supplying 10 patients, to detect an effect size of 15% with SD 2.2%, an intra-class correlation of 0.1, a significance level of 5% (two-sided), a power of 80%, and equal allocation to clusters.

### Statistical analysis

Outcome measures after log transformation will be examined. Mean (SE) values of outcome measures in the intervention and control groups will be compared using the Student's *t*-test. This assumes no within clinic variance; therefore, we will add the following analysis. Namely, in order to assess within-clinic (S^2^_w_) and between- clinic (S^2^_b_) variances, linear mixed models will be used, which included a crude model (Model 1), a baseline-adjusted model (Model 2), and multivariate-adjusted model (Model 3) using individual data.

An "intent-to-treat" (ITT) approach will be performed by the Last Observation Carried Forward (LOCF) method for those subjects who drop out before the end of the 6-month intervention period.

All tests will be done with a significance level 5% (two sided). All statistical analysis will be performed using SAS version 9.2 for Windows (SAS Institute, Inc., Cary, NC, USA).

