## Methods/Design

### Study Design

In Japan, many general practitioners (GPs) have their own medical clinics (primary health centers) in which they provide outpatient medical care in the community. Many patients with T2D receive medical treatment by GPs in these clinics. With the collaboration of GPs, study patients were enrolled in the present study.

The study is a cluster randomized controlled trial with two intervention arms. Each unit of the cluster is comprised of 10 patients sent by a collaborating GP. The cluster design is necessary because an individual randomized controlled study has the disadvantage in that when an individual patient is offered an intervention in the same clinic where a different intervention is offered, discussions of details of the intervention among these patients would result in an intra-correlation. The study period will be 6 months. Figure 1 is a flow diagram of the study design.

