## Discussion

This paper presents a detailed description of a cluster RCT with the aim of investigating the effects of lifestyle education by registered dietitians in medical clinics for patients with T2D compared with the usual care and education provided in such clinics. One of the strengths of this study is that it is the first cluster randomization study in Japan to evaluate an intervention involving a lifestyle education program for such patients in clinics.

Twenty GPs were randomly allocated to an interventional or control group to take part in the current study between September 2007 and December 2010, with each physician recruiting 10 patients to the study. A total of 100 patients will be in each group. That these physicians applied to participate in the study indicated that they were very interested in innovations in the care of patients with T2D and at high risk for T2D. At present in Japan, T2D is managed in the general practice setting. Thus, lifestyle education on diabetes in outpatient clinics has been increasing in Japan. In this setting, GPs and nurses give brief advice on medication management and monitoring of glycemic control, but only a few dietitians are available to offer a diabetes care plan to patients with T2D. Because the success in the treatment of T2D is highly dependent on dietary habits, dietitians can be very helpful to T2D patients in mastering skills for glycemic control. Access to dietitians is easier in a clinical setting than a hospital setting.

There have been studies on lifestyle interventions in T2D in recent years including those with individual randomization [19-22] and cluster randomization designs [23-25]. The point that clinic-based studies have the possibility for contamination bias between intervention and control participants in the same clinic must be considered [13]. Thus, we felt that for our study a cluster randomization design would be best. Furthermore, in order to establish evidence-based nutrition education, examining the effects of the ILIE program presented by registered dietitians in a medical clinic-based study is important.

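### A t-test that, on its natural reading, ignores clinics is named first as a 5% comparison of the arms; at the plan's own ICC its type I error is about 15.5%, and nothing says whether it or the added mixed models decide

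*Protocol article*

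**What the plan says.** All references are to the protocol article.

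- **Study Design:** "The study is a cluster randomized controlled trial with two intervention arms". The unit is the general practitioner's clinic.
- **Sample size:** "We needed the participation of 20 GPs, each supplying 10 patients", with "an intra-class correlation of 0.1, a significance level of 5% (two-sided), a power of 80%, and equal allocation to clusters".
- **Discussion:** "A total of 100 patients will be in each group".
- **Statistical analysis:** after log transformation, "Mean (SE) values of outcome measures in the intervention and control groups will be compared using the Student's" t-test. The next sentence reads "This assumes no within clinic variance; therefore, we will add the following analysis". What is added is a set of linear mixed models on individual data (crude, baseline-adjusted and multivariate-adjusted), introduced as a way to assess the within-clinic and between-clinic variances. The section then applies a two-sided 5% level to every test. No analysis is called primary.

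**The concern.** The design and the sample size both allow for clustering, but the first test named for the arms does not. A t-test on 200 patients treats them as independent, although treatment was assigned to 20 clinics. Its standard error is then too small and its p-value too optimistic whenever patients of one clinic resemble each other, which the plan itself expects.

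Three things in the text make this a fault:

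1. A test whose assumption the authors already doubt stays in the plan as a 5% comparison, for the secondary outcomes as well as HbA1c.
2. The assumption is misnamed. A patient-level t-test allows for variation between patients within a clinic. What it assumes away is variation between clinics.
3. The t-test and three mixed models all stand at 5% with no order among them. If they disagree, the plan does not say which result is the trial's answer, and a positive conclusion could rest on the test that ignores the clinics.

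**Working it through.** **Inputs.** Clinics per arm 10, patients per clinic m = 10, patients per arm 100, ICC 0.1, two-sided 5% (Sample size and Discussion).

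**The plan's own figure.** The 200 patients can be reproduced only with a mean baseline HbA1c, which the article does not give. Assume 8.0%: a 15% relative fall is 0.15 × 8.0 = 1.2 points. With SD 2.2 points, n per arm before clustering is 2 × (2.2 × (1.960 + 0.842) / 1.2)² ≈ 52.8, rounded up to 53. Multiplied by 1.9 this gives 100.7 per arm, which agrees with 100. Other assumed baselines give 131 per arm (7.0%), 116 (7.5%), 89 (8.5%) and 80 (9.0%). So the planned size is consistent with a design effect of 1.9, but does not prove it. Nothing below depends on the baseline, the SD or the effect size.

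**Design effect.** 1 + (m − 1) × ICC = 1 + 9 × 0.1 = 1.9. The 100 patients per arm carry the information of 100 / 1.9 = 52.6 independent patients.

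**Standard error.** The true standard error is √1.9 = 1.378 times the one the patient-level t-test uses. The reported one is 1 / 1.378 = 0.73 of the truth, about 27% too small.

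**Type I error.** 2 × (1 − Φ(1.96 / √1.9)) = 2 × (1 − Φ(1.422)) = 0.155, against 0.05 nominal.

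**Check by simulation.** In 400,000 null trials (10 clinics per arm, 10 patients per clinic, ICC 0.1) the patient-level t-test rejected in 15.6%. A t-test on the 20 clinic means (18 degrees of freedom) rejected in 5.0%.

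**Sensitivity to the ICC**, same formula:

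| ICC | Design effect | Type I error of the nominal 5% test |
|---|---|---|
| 0.01 | 1.09 | about 6% |
| 0.02 | 1.18 | 7.1% |
| 0.05 | 1.45 | 10.4% |
| 0.10 | 1.90 | 15.5% |
| 0.20 | 2.80 | about 24% |

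**The case against.** The strongest reply is that the authors have already dealt with it. The sentence after the t-test commits to mixed models as the remedy, in three versions. Adjusting for baseline and covariates would be pointless if the aim were only to describe variance components, so these models are most plausibly meant to compare the arms too. This stands. A reader might infer that the plan ignores clustering, or that the t-test is its declared primary analysis. The documents support neither: clustered models are planned, and no analysis is labelled primary. That the t-test leads is at most an inference from the order and from the models being described as an addition. The reply does not settle which result governs. If a significant t-test may support a claim, the chance of a false claim is at least that of the t-test alone.

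A second reply is that the t-test might be on clinic means, which would make it valid. Read literally, the remark about within-clinic variance and the contrast with individual data could fit that. But clinic means are never mentioned, and a test on them would not need mixed models as a remedy. The patient-level reading is the natural one, though not certain.

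Third, 0.1 is a planning value, and the ICC of the analysed outcome could be lower. That is fair: at 0.01 the inflation is slight. But 0.1 is the plan's own figure, and at half of it the error is still twice nominal.

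Fourth, how the mixed model's degrees of freedom are computed is ordinary analysis-plan detail. That also stands, and its absence is not part of this point. Nor are standard errors in HbA1c points given here: the outcomes are to be log-transformed, and the article does not make clear on what scale its SD of 2.2% lies.

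**Conclusion.** The point holds as an unsuitable stated analysis with a misnamed assumption and no stated hierarchy. At the plan's own ICC and clinic size, the patient-level t-test has a standard error about 27% too small and a true type I error of about 15.5%, roughly three times nominal.

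The figure rests on the t-test being at patient level, on equal clinics of 10, and on an ICC of 0.1 for the outcome as analysed. For the secondary outcomes no ICC is given, so the direction of the error is the same but its size is unknown.

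It would be too strong to say that the trial as a whole runs at 15.5%. That is the error rate of one of the tests listed. It becomes the trial's minimum error rate only if that test is allowed to carry the conclusion, which the text neither says nor rules out.

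**What to change.** 1. Name one linear mixed model with a random clinic effect as the deciding test and confidence interval for the primary endpoint. The baseline-adjusted Model 2 is a natural choice. Its degrees of freedom should suit 20 clinics; the method can be set in the analysis plan. Describe the other models as supportive.
2. Drop the patient-level t-test, or keep it as description only, with no p-value and no unadjusted standard error, for every outcome. A t-test on the 20 clinic means would serve as a simple cross-check.
3. Correct the sentence on the assumption to say that the t-test assumes no between-clinic variance. If clinic means were intended all along, say so instead.

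The cost is wording; no new data are needed. Intervals become wider than those from the patient-level t-test: at ICC 0.1 and before any gain from baseline adjustment, by a factor of 1.378 from the standard error and 2.101 / 1.972 = 1.065 from the t quantile (18 instead of 198 degrees of freedom), together 1.378 × 1.065 = 1.47. That is the honest precision of 20 clinics.

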**Figure 1 F1:**
[figure not shown]
**Study design**. The file contains an overview of the study design.

The primary endpoint is a change from the baseline value of HbA1c at 6 months. Clinical data including that on the patients' HbA1c value will be obtained from the patient's GP. Lifestyle education by face-to-face and/or telephone sessions will be conducted several times during the study period by a registered dietitian. Data on health behavior and related issues will be gathered continuously by the registered dietitian in charge over a 6-month period beginning at entry. Specifically, behavioral changes will be monitored using an assessment sheet and semi-structured interviews. The study was approved by the Medical Ethical Committee of the National Institute of Public Health in Japan in 2006 (NO.NIPH-IBRA#06005).

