### Study hypothesis

The hypothesis underlying the study is that participation in the intensive dietary education group would decrease the HbA1c value by 15% from baseline (primary endpoint) in the intervention group after 6 months of education whereas such a decrease would not occur in the control group. We assumed that the HbA1c value of the control group would not change. The value of 15% increase in the HbA1c value was decided through reference to a study conducted in the USA [14] and through our experience with a previous survey [18].

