### Outcome measures

The primary outcome measure is a decrease from the baseline HbA1c level after 6 months of education. The difference in the primary endpoint between intervention and control groups is the effect size of the present study. Secondary outcome measures are the differences from baseline for body mass index (BMI), waist circumference, blood pressure, fasting plasma glucose lipid profile, and the difference in energy and nutrition intakes (whole day and each meal) assessed using the FFQW82. Measurements will be made at baseline and at 6 months.

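### With HbA1c scheduled only at baseline and 6 months, LOCF is baseline carried forward: every dropout is analysed as zero change, which generally biases the effect estimate and understates its uncertainty

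*Protocol article*

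**What the plan says.** Study Design defines the endpoint: "The primary endpoint is a change from the baseline value of HbA1c at 6 months". Outcome measures lists the primary and secondary outcomes and then fixes the schedule: "Measurements will be made at baseline and at 6 months". No interim HbA1c is scheduled anywhere. What is collected in between is of another kind: "Data on health behavior and related issues will be gathered continuously by the registered dietitian in charge over a 6-month period beginning at entry".

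For missing outcomes, Statistical analysis gives one rule. The intention-to-treat analysis, it states, "will be performed by the Last Observation Carried Forward (LOCF) method for those subjects who drop out"; this covers anyone who leaves ahead of the 6-month assessment. The same section log-transforms the outcomes and plans a t-test and then linear mixed models on individual data.

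Two further statements bear on the point. On the source of the data: "Clinical data including that on the patients' HbA1c value will be obtained from the patient's GP". On the control arm, under Study hypothesis: "We assumed that the HbA1c value of the control group would not change".

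**The concern.** LOCF is usually defended on the ground that a late on-study value stands in for the final one. With two measurement times there is no such value. A patient who leaves is entered as if seen at 6 months with HbA1c exactly where it started. Analysing patients as randomised does not require this.

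Two things are at stake. First, Outcome measures makes the between-arm difference in HbA1c change the trial's effect size, and that difference is mixed with artificial zeros in proportion to dropout. Secondly, the zeros add to the sample count and carry no variability of their own, so the confidence interval is narrower than the observed patients justify.

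Unequal dropout is plausible here. The intervention arm has 3 or 4 individual sessions and 2-3 further contacts; for the control arm only a first session and usual care are described.

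**Working it through.** **What the rule imputes.** Last available HbA1c = baseline, so imputed change = baseline − baseline = 0. On the log scale, log(baseline) − log(baseline) = 0.

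**Inputs.** From Sample size: 20 GPs with 10 patients each (100 per arm), two-sided 5%, 80% power, and "to detect an effect size of 15% with SD 2.2%, an intra-class correlation of 0.1". Not in the article, so assumed: the baseline HbA1c needed to turn 15% into points, and the dropout rate d.

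**The plan's own figure.** Taken literally, a difference of 15 with SD 2.2 in the same unit needs 1 patient per arm before clustering, so the total of 200 does not follow from the stated inputs alone. If 15% is relative to an assumed baseline of 8.0%, the difference is Δ = 0.15 × 8.0 = 1.2 points:
- n per arm = 2 × (1.960 + 0.842)² × 2.2² / 1.2² = 52.8, rounded up to 53
- design effect = 1 + 9 × 0.1 = 1.9; 53 × 1.9 = 100.7, so 101 per arm and 202 in total

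This is close to 200, so Δ = 1.2 is used as the illustration.

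**Estimate under LOCF**, with equal dropout unrelated to outcome and no change in controls: (1 − d) × Δ.
- d = 10%: 0.90 × 1.2 = 1.08
- d = 20%: 0.80 × 1.2 = 0.96
- d = 30%: 0.70 × 1.2 = 0.84

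**Standard error at d = 20%, ignoring clustering.**
- LOCF variance, intervention: 0.8 × 4.84 + 0.2 × 0.8 × 1.44 = 4.102
- LOCF variance, control: 0.8 × 4.84 = 3.872
- LOCF SE = √((4.102 + 3.872)/100) = 0.282
- SE from the 80 observed patients per arm = √(2 × 4.84/80) = 0.348; ratio 0.81

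**With clustering.** Trials were simulated with 20 clinics of 10, ICC 0.1, SD 2.2, Δ = 1.2 and a t-test on clinic means (18 df), at least 20,000 per setting.

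| Dropout, both arms | LOCF estimate | LOCF 95% CI coverage | Power, LOCF | Power, observed patients |
|---|---|---|---|---|
| 10% | 1.08 | about 94% | 0.724 | 0.726 |
| 20% | 0.96 | about 90% | 0.699 | 0.703 |
| 30% | 0.84 | about 82% | 0.662 | 0.669 |

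At 20% the mean SE is about 0.36 under LOCF against about 0.45 from observed patients, whose interval covers at 95%. With no true effect and no change in either arm, LOCF rejects in 4.8% to 5.1% of trials.

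**Unequal dropout.**
- 20% intervention, 5% control, controls unchanged: estimate 0.80 × 1.2 = 0.96; power about 64% against about 72% from observed patients.
- Same rates, no true difference, both arms assumed to change by −0.5: 0.80 × (−0.5) − 0.95 × (−0.5) = +0.075, a spurious difference against the intervention; type I error about 5.3%.
- 10% intervention, 20% control, no true difference, both arms assumed to change by −0.3: 0.90 × (−0.3) − 0.80 × (−0.3) = −0.03, a spurious difference in its favour.

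**The case against.** The best defence is that the problem may be small or may not arise. No dropout rate is stated; at 5% the estimate would be 0.95 × 1.2 = 1.14. HbA1c comes from the treating GP, so a patient who leaves the education may still have a 6-month value, and LOCF would then never apply. The GP might also hold an unscheduled interim value. This stands as a limit on size, and a condensed article may leave the exact meaning of dropout to the full protocol. It does not rescue the rule: no interim HbA1c is planned, and wherever the rule operates on the stated schedule it imputes zero.

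Three stronger readings are tempting and are not supported.

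- *LOCF costs substantial power even with equal dropout.* Keeping the design effect at 1.9 after imputation gives 65% against 71% at 20% dropout. But zeros spread across clinics also dilute the clinic effect. In the control arm the between-clinic variance is multiplied by 0.8² = 0.64 and the total by 0.80, so the ICC falls to 0.1 × 0.64/0.80 = 0.08. Simulated power is about 70% with either approach. A clear loss appears only with unequal dropout.
- *LOCF produces false positives.* In the settings examined type I error stays near 5%, even with a spurious 0.075-point difference, because that is small against an SE of about 0.39.
- *The bias runs in an unknown direction.* Under the plan's assumption of unchanged controls, and with the intervention lowering HbA1c, it runs towards no effect. A reversal needs unequal dropout and change in both arms.

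The bias also vanishes if dropouts' true mean change is zero in both arms. Nothing in the article supports that for patients who received part of the intervention.

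**Conclusion.** The point holds. It is a stated rule that works badly with the stated schedule, not a detail left to another document. LOCF here is baseline carried forward. The estimate is biased unless dropouts' true mean change is zero, and the interval is too narrow for what the observed patients show about the effect.

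Under the assumptions above, equal dropout of 10%, 20% and 30% turns 1.2 points into about 1.08, 0.96 and 0.84, with coverage of about 94%, 90% and 82%. The harm is to the estimate and its interval; the significance test is largely intact when dropout is equal. The figures rest on an assumed baseline near 8%, assumed dropout rates, dropout unrelated to outcome, and a clinic-level t-test. They show scale and do not predict what this trial will find.

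**What to change.** In Statistical analysis, replace the LOCF sentence with the following:

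1. All enrolled patients are analysed in the arm of their clinic.
2. For patients who stop the education, the 6-month HbA1c is obtained from the GP wherever it exists and consent covers it.
3. For values still missing, the mixed model already planned is fitted by likelihood to the observed baseline and 6-month HbA1c with a clinic effect, assuming data missing at random. Multiple imputation that respects clinic is an alternative.
4. Baseline carried forward is kept, if at all, as a sensitivity analysis labelled as such.

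The cost is a change of wording, modest chart retrieval from GPs who already supply the data, some programming, and a somewhat wider interval. The wider interval reflects the information actually collected.

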## Discussion

This paper presents a detailed description of a cluster RCT with the aim of investigating the effects of lifestyle education by registered dietitians in medical clinics for patients with T2D compared with the usual care and education provided in such clinics. One of the strengths of this study is that it is the first cluster randomization study in Japan to evaluate an intervention involving a lifestyle education program for such patients in clinics.

Twenty GPs were randomly allocated to an interventional or control group to take part in the current study between September 2007 and December 2010, with each physician recruiting 10 patients to the study. A total of 100 patients will be in each group. That these physicians applied to participate in the study indicated that they were very interested in innovations in the care of patients with T2D and at high risk for T2D. At present in Japan, T2D is managed in the general practice setting. Thus, lifestyle education on diabetes in outpatient clinics has been increasing in Japan. In this setting, GPs and nurses give brief advice on medication management and monitoring of glycemic control, but only a few dietitians are available to offer a diabetes care plan to patients with T2D. Because the success in the treatment of T2D is highly dependent on dietary habits, dietitians can be very helpful to T2D patients in mastering skills for glycemic control. Access to dietitians is easier in a clinical setting than a hospital setting.

There have been studies on lifestyle interventions in T2D in recent years including those with individual randomization [19-22] and cluster randomization designs [23-25]. The point that clinic-based studies have the possibility for contamination bias between intervention and control participants in the same clinic must be considered [13]. Thus, we felt that for our study a cluster randomization design would be best. Furthermore, in order to establish evidence-based nutrition education, examining the effects of the ILIE program presented by registered dietitians in a medical clinic-based study is important.

There are some limitations in this study design. Firstly, the success of this program is to some degree dependent on the dietitian's skill. To address this issue, we have developed a training process for the registered dietitians before the start of the randomization study. Educations in implementing the program are therefore important. Furthermore, the assessment sheet with items ranked according to priority helps standardization of advice by registered dietitians. Secondly, only patients were blinded to the groups. In order to avoid selection bias, we asked GPs to recruit all the patients in turn. Furthermore, we used HbA1c as the primary outcome, which is an objective measure. Although we cannot deny the possibility of the bias, it may be small.

The study began in September 2007 and the enrollment of patients will be completed in December 2010. The 6-month followed up period for all patients will end in June 2011. If this study appears to have positive effects, the behavioral intervention of T2D might also be implemented by other GPs in Japan.

